# Continuous passive motion and physical therapy (CPM) versus physical therapy (PT) versus delayed physical therapy (DPT) after surgical release for elbow contractures; a study protocol for a prospective randomized controlled trial

**DOI:** 10.1186/s12891-017-1854-0

**Published:** 2017-11-22

**Keywords:** Stiff elbow, Operation, Surgery, Rehabilitation, Continuous passive motion, Physical therapy, Randomized controlled trial

## Abstract

**Background:**

The elbow is prone to stiffness after trauma. To regain functional elbow motion several conservative- and surgical treatment options are available. Conservative treatment includes physical therapy, intra-articular injections with corticosteroids and a static progressive or dynamic splinting program. If conservative treatment fails, an operative release of the posttraumatic stiff elbow is often performed. The best Evidence-Based rehabilitation protocol for patients after an operative release is unknown to date and differs per surgeon, hospital and country. Options include early- or delayed motion supervised by a physical therapist, immediate continuous passive motion (CPM), (night) splinting and a static progressive or dynamic splinting program.

**Methods/design:**

The SET-Study (Stiff Elbow Trial) is a single-centre, prospective, randomized controlled trial. The primary objective of this study is to compare the active Range of Motion (ROM) (flexion arc and rotational arc) twelve months after surgery between three groups. The first group will receive in-hospital CPM in combination with early motion Physical Therapy (PT) supervised by a physical therapist, the second group will receive only in-hospital early motion PT supervised by a physical therapist and the third group will receive outpatient supervised PT from postoperative day seven till ten. Secondary outcome measures will be Patient Reported Outcome Measures (PROMs) including the Mayo Elbow Performance Score (MEPS), the Oxford Elbow Score (OES), the quick Disabilities of Arm, Shoulder and Hand (qDASH) score, Visual Analogue pain Scale in rest and activity (VAS), Pain Catastrophizing Scale (PCS), the Short Form (SF)-36, the Centre for Epidemiological Studies Depression Scale Revised (CESD-R) and the Work Rehabilitation Questionnaire (WORQ) for the upper limb.

**Discussion:**

A successful completion of this trial will provide evidence on the best rehabilitation protocol in order to (re)gain optimal motion after surgical release of the stiff elbow.

**Trial registration:**

The trial is registered at the Dutch Trial Register: NTR6067, 31–8-2016.

## Background

All types of post-operative treatment rehabilitation protocols for the elbow are used all over the world: from three in-hospital days of costly continuous passive motion (CPM) and physical therapy (PT) to an outpatient one-day procedure with delayed PT.

The posttraumatic elbow is prone to stiffness [1–6]. After trauma, up to 12 % of all elbows end up with a decreased range of motion (ROM) requiring surgical release [7], however the etiopathogenesis remains largely unknown [6]. According to Morrey and colleagues, most activities during the day can be accomplished with 100 degrees of ROM regarding to flexion-extension arc (30 to 130) and 100 degrees of forearm rotation (50 to 50). [8] Nevertheless, more recently, others reported that functional elbow ROM necessary for activities of daily living may be greater than previously concluded. Contemporary tasks, i.e. as using a computer mouse and keyboard, appear to require greater pronation than drinking from a glass, and using a cellular telephone usually requires greater flexion than for example eating with fork and knife [9].

To regain functional elbow motion several conservative and surgical treatment options are available [6]. Surgical contracture release can be performed open or arthroscopically depending on the type of deformity of the posttraumatic elbow and surgeons’ preference. The results of both techniques are largely comparable, but the amount of complications seems to rise with the extent of the surgical procedure [1, 10, 11]. Recurrence of elbow stiffness up to 37% remains a point of concern and is unrelated to the techniques used to date [10, 12].

Post-operative rehabilitation protocols after operative release for a patient with a posttraumatic stiff elbow include: PT, CPM or a static progressive or dynamic splinting program as prospectively studied by our group [12–14]. In a retrospective study, Lindenhovius et al. previously found that CPM may be redundant [15]. Moreover, from basic science perspective, it theoretically seems that due to early expression of myofibroblasts after trauma that are susceptible to traction (i.e. biomechanical stimuli), it seems that early motion or traction as provided by CPM should be avoided until after the acute phase in order to prohibit the myofibroblasts to produce abundant extra-cellular matrix. This hypothesis is theoretical, based on preliminary histology studies by our group [16]. In contrast to CPM and splinting programs, in all previous described studies physical therapy plays a role and is therefore always included in rehabilitation protocols.

However, the best Evidence-based rehabilitation protocol regarding additional treatment and timing of physical therapy for patients after an operative release is unknown and differs per surgeon, hospital and country. The most recent review on this topic does not show a clear clinical benefit of any of the respective post-operative rehabilitation protocols [6]. However, no randomized controlled trials were included. Therefore, we study which type of rehabilitation protocol after elbow capsule release at one year after surgery is most effective in terms of range of motion (ROM) in a randomized controlled trial. The potential health care efficiency gain consists of more homogeneity in rehabilitation after elbow capsule release and less costs regarding in-hospital stay. Hence, unnecessary treatments could be avoided and a more universal treatment can be established.

## Methods

### Study design

The SET-study is a three-arm, prospective, single-centre, randomized controlled trial with twelve months of follow-up. One teaching hospital in the Netherlands will participate. Patient will be included in one of the three post-surgical release rehabilitation arms after index surgery for stiff elbow:In-hospital Continuous Passive Motion with Early Motion Supervised Physical Therapy (CPM)In-hospital Early Motion Supervised Physical Therapy (PT)Outpatient Supervised Physical Therapy from postoperative day 7–10 (DPT)

In our hospital, the gold standard as rehabilitation protocol after capsule release of the stiff elbow includes CPM with physical therapy. Therefore, the control-group of our study is group one (CPM-group).

### Recruitment and consent

All patients presenting to our outpatient Orthopaedic Elbow clinic with a posttraumatic stiff elbow that plateaus in their post-fracture rehabilitation program after more than 6 months after trauma, who meet the inclusion criteria will be invited to participate in the trial. Each patient will receive a Computed Tomography (CT-) scan, since this is part of our usual care.

The treating surgeon or resident will introduce the trial to the patient and address the patient’s questions. Information will be handed to the patient to read at home. If the patient is willing to participate, written informed consent is required and will be obtained. Participants will be given a copy of the consent form and will be informed that their participation is voluntary and that they can withdraw from the study at any time. Participants may take as long as they like to consider participation, provided that they still meet all eligibility criteria stated below.

After providing informed consent, each patient will be randomly assigned to the CPM- PT- or DPT-group on the basis of a random sequence determined by a computerized random-number generator based on our enrolment goal of 90 patients (Castor Electronic Data Capture (EDC), Ciwit BV, Amsterdam, the Netherlands).

### Study population

Patients with the following inclusion criteria are eligible for enrolment*:*
Age between 18 and 65 yearsFlexion-extension arc of <100° or a contracture >30° compared to contralateral sideOpen or arthroscopic surgical treatment receivedMore than 6 months after traumaUnsuccessful conservative treatmentAble to read and write in DutchProvision of informed consent by patient

If any of the following criteria apply, patients will be excluded:Inflammatory diseases (i.e. rheumatoid arthritis, psoriatic arthritis, or reactive arthritis)Patients with any other elbow pathology (i.e. spastic contracture)Neck pain or shoulder pain or other chronic widespread pain syndromesWound problemsInability to cooperate with a structures rehabilitation protocolBurn-related contracturesA total elbow or interposition arthroplasty (either planned or in place)

### Intervention

Patients that are assigned to the ‘CPM’ group will receive in-hospital CPM during one hour in combination with supervised physical therapy, both three times a day, the first three days (in hospital), starting two till four hours after surgery depending on anaesthesia and supervised physical therapy from day three till day 14 postoperative (at home). Patients that are assigned to the ‘PT’ group will receive in-hospital supervised physical therapy three times a day the first three days, start two till four hours after surgery and supervised physical therapy from day three till day 14 postoperative at home. Patients that are assigned to the ‘DPT’ group will receive outpatient physical therapy from postoperative day 7–10 till 14 and will be discharged from the hospital immediately after surgery. In-hospital physical therapy includes both active and passive exercises, manual manipulation of rotations and angular mobilization of the ulnohumeral joint, with a duration of 10 min three times a day; moreover, patients will be invited to practice themselves as well. Thereby, the patient will be provided wrist- and hand exercises to improve circulation and to prevent oedema.

After discharge from the hospital, all patients of the three groups are handed out the same physical therapy program for the first six months. After the first 14 days, all patients will continue with physical therapy, which is recommended three till four times a week the first 4 months. Thereafter, the amount of physical therapy sessions can be reduced, but sessions themselves can be extended with use of weights. Patients are allowed to choose an outpatient physical therapist by themselves. In addition, patients are asked to fill in Patient Reported Outcome Measures (PROMs) during every appointment at the outpatient clinic.

### Outcome measures

The primary outcome measure is the active ROM (flexion, extension, pronation, supination) of both elbow joints, measured with a universal goniometer, one year after surgery. The references for measuring the ROM are the acromion and the styloid process of the radius, with the lateral epicondyle as central point of the rotation.

Secondary outcome measures are PROMs which consist of;The Oxford Elbow Score (OES) [17, 18], which reflects both function and pain following elbow surgery. The OES consists of three domains; pain, function and social-psychological. Each domain comprises of 4 questions with 5 response options per question. Each response is scored 0 to 4, with 0 representing greater severity. Scores for each domain are calculated as the sum of each individual item score within that domain. These scores are then converted to a metric score between 0 and 100 (a lower score represents greater severity). The Minimal Clinically Important Difference (MCID) for the OES is 10 points [19].The Mayo Elbow Performance Score (MEPS) [20], which is based on 4 domains (pain, range of motion, stability and elbow function). A total score between 90 and the maximum 100 points is considered excellent; 75–89 is good; 60–75 is fair and less than 60 points is poor. The MCID for the MEPS is 15 points [21].The quick Disabilities of Arm, Shoulder and Hand (qDASH) score [22–24], which is scored in two components: the disability/symptom section (11 items, scored 1–5) and the optional high-performance sport/music or work modules (four items, scored 1–5). The quick-DASH is designed to measure physical function and symptoms in patients with any or several musculoskeletal disorders of the upper limb. The MCID for the qDASH is 10 points [25].The Visual Analogue pain Scale in rest and activity (VAS) [26], which is a one-dimensional measure of pain intensity scored between 0 and 100. 0 is no pain and 100 is the maximum of pain. The MCID for the VAS 0–100 is 14 points [27].The Pain Catastrophizing Scale (PCS) [28], which consists of 13 items reflecting catastrophic thinking in relation to pain. The PCS total scores ranges from 0 to 52, in which a higher score is related to an experienced higher level of physical and emotional distress associated with the pain condition. The MCID for the PSC is not established.The Short Form (SF)-36 [29], which measures the quality of life. The SF-36 consists of eight scaled scores, which are the weighted sums of the questions in their section. Each scale is directly transformed into a 0–100 scale on the assumption that each question carries equal weight. The lower the score the more disability. The MCID for the SF-36 is not established.Centre for Epidemiological Studies Depression Scale Revised (CESD-R) [30], which consists of 20 items, is a screening test for depression and depressive disorder. Patients are asked to fill in how many times they were experiencing specific symptoms (not at all or less than one day = 0, 1–2 days = 1, 3–4 days = 2, 5–7 days = 3, nearly every day for 2 weeks). The sum of the answers in combination with DSM criteria is representative for the severity of the depression. The MCID for the CESD-R is not established.The Work Rehabilitation Questionnaire (WORQ) for the upper limb is a questionnaire specific for work-related limitations in patients with upper extremity musculoskeletal disorders. The content includes four categories: exertion, dexterity, handling tools & equipment, and mobility. Patients are asked to fill in how difficult it was to perform several activities while performing their job (caused by symptoms of the affected upper extremity). Patients have to rate their difficulty on a 6-point scale: 0 = not applicable (in my job), 1 = not at all, 2 = slightly, 3 = moderately, 4 = very, 5 = extremely, or I cannot do this. The MCID for the WORQ is not established.

### Study procedures

Clinical assessment will be performed preoperatively (baseline), during surgery, at day three, at day ten, eight weeks, five months and one year after surgery. A link to all (online) questionnaires will be sent to the patients at baseline and one year after surgery. In addition, a link of the qDASH, OES, VAS and MEPS will be sent eight weeks and five months after surgery. An independent and blinded researcher will perform postoperative assessment (Fig. 1).

**Fig. 1 Fig1:**
[figure not shown]
Timeplan study procedures of the SET-study

### Sample size calculation

The primary study question addresses improvement in active elbow flexion-extension arc and pronation-supination arc at one year. A power analysis indicated that a total sample size of 72 patients (24 patients in each cohort) would provide 80% power (b = 0.20, a = 0.05) to detect a clinically relevant difference of ten degrees in improved flexion arc. To account for a possible loss to follow-up of 20 to 25%, we anticipate enrolling 30 patients in each cohort; 90 patients in total for this study.

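### Enrolling 30 per arm allows for 20% loss to follow-up, not for the stated 20 to 25%: at 25% loss 67 to 68 of the required 72 patients remain

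*Protocol article*

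**What the plan says.** The protocol article, under Sample size calculation, states the requirement in terms of evaluable patients: "a total sample size of 72 patients (24 patients in each cohort) would provide 80% power". The target is "to detect a clinically relevant difference of ten degrees in improved flexion arc", at an alpha of 0.05. The sentence that follows turns this into an enrolment figure: "To account for a possible loss to follow-up of 20 to 25%, we anticipate enrolling 30 patients in each cohort; 90 patients in total".

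The section on recruitment and consent repeats the total; the random sequence there is "based on our enrolment goal of 90 patients". The article gives no rule for replacing lost patients or topping up enrolment. Under Statistical analysis, the primary comparison is an ANOVA of the three groups on the one-year change in the flexion-extension arc.

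**The concern.** The enrolment sentence offers 30 per arm as an allowance for a range of losses. To do that, 30 per arm must still leave 24 per arm at the top of the range. It leaves 24 only at the bottom, so the sentence claims a protection that the design does not have.

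What is at stake is how the result will be read. The trial asks, among other things, whether in-hospital continuous passive motion is redundant. If no difference is found, readers will look at the planned power to judge how much that says. With losses in the upper part of the stated range, they would credit the trial with 80% power that its own figures do not secure.

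**Working it through.** **Inputs** (Sample size calculation, unless noted)
- Evaluable patients required: 72, or 24 in each of 3 arms
- Power and alpha: 80% and 0.05
- Loss to follow-up: 20 to 25%
- Enrolment: 90, or 30 per arm (total repeated under Recruitment and consent)
- Primary test: three-group ANOVA (Statistical analysis)
- Standard deviation and pattern of the three means: not given, so handled below by calibration

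**Step 1. Reproduce the plan's figure.** Enrolment = evaluable / (1 − loss).
- At 20% loss: 72/0.80 = 90, and per arm 24/0.80 = 30. This matches the plan exactly, with nothing to spare.

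**Step 2. The upper end of the range.**
- Needed at 25% loss: 24/0.75 = 32 per arm, 3 × 32 = 96 in total, which is 6 more than planned.
- Left from 90 at 25% loss: 90 × 0.75 = 67.5 (22.5 per arm). The shortfall is 72 − 67.5 = 4.5 patients, and 4.5/72 = 6%.
- Largest loss that still leaves 24 per arm: 1 − 24/30 = 20%.

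**Step 3. What this does to power.** For the three-group ANOVA with N evaluable patients and Cohen's effect size f, power is the probability that a noncentral F variable with 2 and N − 3 degrees of freedom and noncentrality N × f² exceeds the 5% critical value. No standard deviation is stated, so f is back-solved from the plan's own power claim in two ways:
- Case A: 72 patients give exactly 80%. Then f = 0.374.
- Case B: 24 per arm was rounded up from just over 23, so 69 patients give almost exactly 80%. Then f = 0.382, and power at 72 is 81.8%.

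| Loss from 90 | Evaluable | Power, case A | Power, case B |
|---|---|---|---|
| 20% | 72 | 80.0% | 81.8% |
| 22.5% | 69.75 | 78.6% | 80.5% |
| 25% | 67.5 | 77.1% | 79.0% |

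Rounding 67.5 to whole patients changes little: 67 and 68 give 76.7% and 77.4% in case A, and 78.7% and 79.4% in case B.

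**Step 4. Does the choice of test matter?** Calibrated as in case A, at 22.5 per arm a pairwise t-test gives 77.3%, a pairwise normal approximation 77.4%, and a Bonferroni-adjusted pairwise test 77.0%. The answer hardly depends on the test.

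**Step 5. The direction without any standard deviation.** If 24 is the smallest whole number per arm that reaches 80%, then 23 per arm does not reach it, and 22.5 per arm does not either.

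**The case against.** The strongest reply is that the effect is too small to matter. The article calls the loss possible, the lower end is covered exactly, and at 22.5% loss power is between 78.6% and 80.5%. In case B, power stays at about 80% until 69 patients remain, a loss of 21/90 = 23.3%. A change of 1 to 3 points at the far end would not alter the design. All of this stands. It limits the point to the wording of one sentence, but does not make that sentence true at 25%.

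The Ethical considerations section says that patients who miss a follow-up visit will be invited back at no cost. That may make the upper end less likely, but it does not make 90 enough if the upper end is reached. The intention-to-treat rule does not help either. The article's example concerns crossover between arms, not missing one-year measurements, and the sample size section itself treats lost patients as lost to the calculation.

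A reader might infer more than the document supports, in four ways:
- *The 80% power claim is wrong.* That claim is tied to 72 evaluable patients and is not shown to be wrong. Only the allowance for loss fails, and only above 20%.
- *Power falls to 77% whatever standard deviation was assumed.* This holds only if 24 per arm gives exactly 80%. Rounding up to whole patients allows up to about 79%.
- *The planners marked up 24 by 25% (24 × 1.25 = 30) instead of dividing by 0.75.* The figure 30 also comes from correct division at 20%, and the range may express the same six patients in two ways (6/30 = 20%, 6/24 = 25%). The article does not say which.
- *The missing standard deviation is part of the error.* A journal article may leave it to the full protocol. Here its absence only means that the power figure must be given as a range.

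**Conclusion.** The point holds in a limited form. The shortfall in patients is certain, since it follows from the article's own figures. The power figure of about 77 to 79% at 25% loss is conditional. It assumes that 24 per arm is either exactly the size for 80% or the next whole number above that size, and that the effect and variability are as planned. Within those assumptions power at 25% loss is 1 to 3 points below 80%.

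This is an inaccurate statement that should be corrected. It is not a flaw that threatens the trial.

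**What to change.** Keep the enrolment goal of 90 and reword the one sentence under Sample size calculation, for example: *Enrolling 30 patients per arm (90 in total) allows for 20% loss to follow-up, leaving 72 evaluable patients and 80% power; if loss reaches 25%, about 67 patients will be evaluable and power will be about 77 to 79%.* The sponsor, who holds the original calculation, can replace that range with a single figure.

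The cost is one sentence. The stated power becomes slightly less favourable at the upper end of the loss range, and no patients, visits or analyses are added. The alternative is to make the existing sentence true by enrolling 32 per arm, 96 in total. At the accrual of 4 patients per month expected in the Discussion, that is 6/4 = 1.5 more months, and the goal of 90 under Recruitment and consent would have to change as well. For so small a shortfall, rewording is the proportionate choice.

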### Statistical analysis

The data will be presented in line with the SPIRIT statement. Analyses will be performed according to the intention-to-treat principle, according the following example: when a patient crossed over from the ‘CPM’ group, to the ‘PT’ group (i.e. still having supervised physical therapy, but the patient refuses CPM, or does not tolerate CPM), analysis will be according to initial randomization, with this patient in this particular example still being analyzed in the ‘CPM group’ although the patient did not receive CPM, he or she will be analyzed according the intention to treat in this cohort. After completing the trial, a post-hoc power analysis will be performed again, to address and account for alpha post-RCT with known standard deviation in our three study groups.

Patients’ baseline characteristics will be compared between the three groups. Depending on the distribution of the gathered data, Chi-square tests or Fisher’s Exact tests will be used for categorical variables, and ANOVA or Kruskal Wallis tests for continuous variables.

For our primary outcome, the improvement in active elbow flexion-extension arc in degrees after one year, an ANOVA will be performed to compare the three groups. For the other time-points and the other continuous outcome parameters (flexion, extension, flexion contracture, forearm rotation, pronation, supination, qDASH scores, OES scores, MEPS scores, SF-36 scores, CESD-R scores, VAS pain scores, PCS scores and WORQ scores and number of additional surgeries) also the changes compared to the pre-randomization scores will be compared between cohorts using ANOVAs. An alpha correction for multiple comparisons on the same secondary outcome measure will be applied.

Differences in categorical outcome parameters (MEPS) will be compared between the groups at each time-point using the Chi-square test for trend. Furthermore, the association between the arc of elbow flexion and extension and the qDASH scores will be analyzed at enrolment and at the six- and twelve-month evaluations using Spearman correlation. Also in these cases an alpha correction for multiple comparisons on the same secondary outcome measure will be applied.

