## Discussion

To date there have been no prospective randomized trials comparing rehabilitation protocols after surgical release of a stiff elbow. The SET-study will compare management of these rehabilitation protocols by using in-hospital CPM in combination with early motion supervised PT, in-hospital early motion supervised PT without CPM and outpatient delayed supervised PT. Based upon current scientific literature, there is no clear preference for one of the treatments regarding the increase of ROM after surgery. CPM in elbow surgery may be redundant [15] and also in other joints such as the knee, the use of CPM as after treatment seems ineffective and unnecessary [32].

The different treatment options are regularly applied for posttraumatic elbow contractures in the participating institution and all surgeons participating in this study are familiar with the procedure. Patients in all cohorts are likely to benefit from treatment. The motivation for the study is that unnecessary treatment burden for patients (prolonged hospital stay, because of CPM sessions) as well as redundant costs for society can be avoided, a more universal Evidence-Based method of treatment can be established and the quality of the care can be improved. Regarding to potentially less healthcare costs, a cost-effectiveness analysis will be performed in a separate study.

Patient enrolment will start in March 2017 and we expect to enroll 4 patients per month. Considering the one-year follow-up, publication of data will be expected in 2020.

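### The planned post-hoc power analysis cannot account for alpha, and a non-significant ANOVA would not show that CPM or the hospital stay is redundant; confidence intervals read against 10 degrees should replace it

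*Protocol article*

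**What the plan says.** The Statistical analysis section of the protocol article compares one-year improvement in the active flexion-extension arc across the three arms with a single ANOVA. It also commits to a further step once follow-up is complete: "a post-hoc power analysis will be performed again, to address and account for alpha post-RCT with known standard deviation in our three study groups".

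The Sample size calculation section gives 24 patients per arm, 80% power and alpha 0.05, "to detect a clinically relevant difference of ten degrees in improved flexion arc". No SD is given. On attrition it says: "To account for a possible loss to follow-up of 20 to 25%, we anticipate enrolling 30 patients in each cohort".

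The Study design section makes CPM the control, as the hospital's standard. The Background asks which protocol is most effective for range of motion and names lower in-hospital cost as a potential gain. The Discussion says that "CPM in elbow surgery may be redundant" and gives as motivation that "unnecessary treatment burden for patients (prolonged hospital stay, because of CPM sessions) as well as redundant costs for society can be avoided". The article states no non-inferiority or equivalence hypothesis, no margin, and no rule for interpreting a non-significant result.

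**The concern.** There are two linked problems.

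- **The post-hoc step cannot do what it is said to do.** Alpha is a design choice fixed before the data. Recomputing power with the observed SD neither adjusts it nor says which true differences remain compatible with the results.
- **The stated test does not answer one of the questions that motivate the trial.** A difference test can show that one protocol is better than another. If it is non-significant, it does not show that CPM or the inpatient stay adds nothing. The only further step described is the power calculation, which does not fill that gap.

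At stake is a practical decision to drop the local standard. A true 10-degree loss, which the article itself calls clinically relevant, could sit behind a non-significant ANOVA.

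**Working it through.** **Inputs from the article:** 24 evaluable patients per arm (72 in total), alpha 0.05 (two-sided assumed), power 80%, difference 10 degrees, three arms, ANOVA.

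**Input missing:** the SD of improvement. The figure of 72 therefore cannot be reproduced directly. Solving a two-sided two-sample t-test (24 per arm, 10 degrees, 80% power) for the SD gives 12.1. Other routes give 12.4 (normal approximation), 12.6 (ANOVA, means 0/0/10) and 10.9 (ANOVA, means 0/5/10). I use 12.1, with 15 and 20 as a range; all three are assumptions. The enrolment figure does reproduce at 20% loss: 72 / (1 − 0.20) = 90.

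**Step 1. Reading A of the post-hoc step: power at the observed effect.** With df 2 and 69 the critical F is 3.13. Observed power is P(F′(2, 69; λ = 2·F_obs) > 3.13), so it depends only on F_obs, and hence only on p.

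| ANOVA p | F_obs | Observed power |
|---|---|---|
| 0.05 | 3.13 | 58% |
| 0.10 | 2.38 | 47% |
| 0.20 | 1.65 | 34% |
| 0.50 | 0.70 | 16% |

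On this reading the calculation adds nothing to the p-value.

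**Step 2. Reading B: power at 10 degrees with the observed SD.** With one arm 10 degrees from the other two, the squared deviations of the means from their average sum to 66.7, so λ = 24 × 66.7 / SD². The miss rate is 1 − power.

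| SD | λ | Power | Non-significant despite a true 10-degree difference |
|---|---|---|---|
| 12.1 | 10.9 | 83% | 17% |
| 15 | 7.1 | 64% | 36% |
| 20 | 4.0 | 40% | 60% |

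With means 0/5/10 the miss rates are 29%, 49% and 69%. This quantity is not a function of p; it reflects the precision achieved. But it is the same wherever the estimates fall, so it cannot say whether a 10-degree loss has been excluded. Nor does it alter alpha.

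**Step 3. What an interval gives.** For a pairwise difference with pooled variance, half-width = t(0.975, 69) × SD × √(2/24), with t = 1.995.

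- SD 12.1: 1.995 × 3.49 = 7.0 degrees
- SD 15: 1.995 × 4.33 = 8.6 degrees
- SD 20: 1.995 × 5.77 = 11.5 degrees

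At SD 20, an interval centred on zero still contains a 10-degree loss.

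**Step 4. What the interval rule can deliver if the arms are truly equal.** For one comparison, the chance that the lower 95% limit (PT or DPT minus CPM) lies above −10 is P(t′ > 1.995), where t′ is noncentral t with df 69 and noncentrality 10 / SE. For both comparisons, the two differences share the CPM mean (correlation 0.5) and the pooled variance; this was simulated.

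| SD | One comparison | Both comparisons |
|---|---|---|
| 12.1 | about 80% | about 70% |
| 15 | 62% | 47% |
| 20 | 40% | 24% |

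The 80% at SD 12.1 is partly built in, because that SD was derived from 80% power at the same n and the same 10 degrees. At an illustrative 5-degree margin, the one-comparison figure falls to 28–35% for SD 12.5 down to 11.

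**The case against.** Several points on the other side stand and limit the finding.

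- A reader might infer that the planned power figure is merely the p-value in another form. That holds only under Reading A. The text says the analysis is done again with a known SD, which more naturally means repeating the 10-degree calculation. That figure does carry information about precision.
- A reader might infer that a null result will be interpreted through the power analysis. The article does not say so: the step is planned whatever the result.
- A reader might infer that the trial is built to prove CPM redundant. Its formal question is which protocol is most effective, and the Background gives a biological reason why early motion might do harm. A significant result favouring PT or DPT would bear on CPM without any margin. Redundancy is part of the motivation, not the stated hypothesis, so the missing margin is not an internal contradiction.
- Pairwise contrasts and intervals may be set out in a full protocol or SAP that is not shown. Their absence from the article is not the defect.

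These points do not rescue the sentence itself. It assigns to a power calculation a task that no power calculation can perform, and a later SAP would have to drop or replace it. It also remains true that a non-significant ANOVA would not establish redundancy.

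**Conclusion.** The concern holds in this form. The stated purpose of the post-hoc power analysis is invalid on either reading, and neither reading substitutes for a confidence interval. The one primary inference given, an omnibus difference test, would not support a redundancy conclusion if it were non-significant: the risk of missing a true 10-degree difference in one arm is about one in six at the SD implied by the design, and rises to 60% at SD 20. All these figures assume 24 evaluable patients per arm, a common SD and two-sided alpha 0.05, and no SD is stated in the article.

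The documents do not support saying that the sponsor intends to read a null result this way. Nor is the interval rule achieved with the design's 80% power throughout: that figure applies to one comparison at the back-solved SD and drops to about 70% when both must succeed. This should be corrected, but it does not invalidate the design.

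**What to change.** 1. Delete the post-hoc power sentence.
2. Pre-specify 95% confidence intervals for PT minus CPM and DPT minus CPM in 12-month flexion-arc improvement, reported whatever the ANOVA result. PT minus CPM addresses CPM itself, since both arms stay in hospital. DPT minus CPM addresses dropping CPM, early therapy and the stay together.
3. State that a non-significant result supports redundancy only where the relevant interval excludes a loss as large as the trial's own 10 degrees, or a smaller margin if one is justified, and is otherwise inconclusive. Using the full 10 degrees as the margin needs its own justification.

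**Cost:** a few lines of text and no extra patients. The sponsor gives up claiming no difference when the interval is wide, and must accept that the result may be inconclusive even if the arms are truly equal: about 20% of the time for one comparison and 30% for the pair at SD 12.1, and more often at a larger SD or with a smaller margin.
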